##### Component 6: Live Group Classes

Live 75-minute group classes are offered to participants over the course of the year, with more instruction towards the beginning of the intervention period. Classes are conducted weekly for the first 6 weeks, biweekly for the next 34 weeks, and monthly for the last 12 weeks (25 total). Participants attend classes together as a cohort. The class curriculum follows themes from the Mindful Walking curriculum (component 4), including guided mindful walking, and also incorporates mind–body exercises from the video library (component 5). Classes begin and end with facilitated group discussion of class themes, exploration of barriers and successes with regard to step-count goals, and general check-ins. Classes are taught by experienced instructors who have led classes in our prior mind–body exercise clinical trials for over 10 years.

##### Component 7: Earn Your Stars

Earn Your Stars is an extrinsic motivational reward system to incentivize participants to stay engaged with the website content and their step-count goals. Participants can earn up to 3 stars a day for each of the following: reaching daily step-count goal, watching a video, clicking on Motivational Messages or Educational Tips. The star counter displays the total star accumulation on the individual’s home page. Small prizes (eg, US $5 gift cards) are given out when participants reach >100 and >500 stars.

### Phase 2: Pilot Randomized Controlled Trial

In a pilot randomized controlled trial, we are testing the delivery of the multimodal intervention versus usual care control in patients with COPD and/or HF. In addition to study and intervention feasibility and acceptability measures, we will explore the mediating components of the mind–body exercise approach articulated in our conceptual model and assess clinically meaningful changes in self-efficacy and overall physical activity over the long term of 1 year. At Beth Israel Deaconess Medical Center, 42 participants with COPD and/or HF have been randomized in a 2:1 ratio to participate in the 1-year Mindful Steps program or to receive usual care (including verbal and written instructions to exercise).

#### Study Population and Recruitment

The inclusion criteria include the following: age over >40 years; clinical diagnosis of COPD, defined as either a ratio of forced expiratory volume in one second (FEV_1_) to forced vital capacity <0.70 or chest computed tomography evidence of emphysema, and/or clinical diagnosis of HF syndrome (with left ventricular systolic dysfunction or preserved ejection fraction, and New York Heart Association Class 1-3); medical clearance from a provider to participate in an exercise program; an active email account with the ability to check email at least weekly; and access to a computer with an internet connection, USB port, and Windows. Meanwhile, the exclusion criteria include the following: self-reported COPD or HF exacerbation in the previous 2 weeks; inability to ambulate; clinical signs of unstable cardiovascular disease; hypoxemia during 6-minute walk test (oxygen saturation <85% with supplemental oxygen); inability to collect at least 7 of 14 days of baseline step counts; current participation in a cardiac or pulmonary rehabilitation program.

To identify potential participants, we searched hospital registries, screened physician schedules, solicited direct physician referrals through email, and used targeted patient advertising (paper flyers, digital screen ads, in-person presentations) in primary care or specialty clinics at Beth Israel Deaconess Medical Center and pulmonary rehabilitation clinics in the community. This was followed by opt-in mailing and telephone outreach conducted by our research assistants.

#### Randomization and Intervention Delivery

As in prior studies, we used a 14-day run-in period of pedometer (Fitbit) use requiring at least 7 days of valid data (>200 steps per day) as a criterion for participants to be eligible for randomization. As the sample size is relatively small, we will use blocked randomization with varying block sizes and a computer-generated sequence of random numbers with a concealed and unpredictable allocation scheme.

Participants in the Mindful Steps intervention will receive the pedometer, access to the Mindful Steps website, and a schedule of in-person mind–body exercise classes as described in detail previously in this paper. All participants will continue pharmacological treatment and receive care through their usual providers. Participants in both groups will also receive an education handout from Harvard Health Publishing and Harvard Medical School titled “Walking for Health,” which includes information on the health benefits of walking, how to get started on a walking program, and specific walking workouts [104].

#### Study Assessments

Table 2 outlines study feasibility and intervention acceptability and adherence measures that are being tracked to inform a future larger trial.

**Table 2 table2:** Study feasibility and intervention acceptability and adherence measures.

Outcomes and measures		Description
**Study feasibility**		
	Recruitment	Track recruitment rate by site and strategy (eg, clinic visits, mailings, advertisement sites, involvement of physician, etc.)
	Retention	Track retention rate with acceptable retention defined as <20% dropouts
**Intervention acceptability**		
	Qualitative interview	Semistructured interview at 6 months (in person) and 12 months (by phone) to assess patient experience, understand helpful components of the multimodal intervention, and specifically explore themes related to conceptual model
	Physical Activity Enjoyment Scale [105]	8-item shortened version used to assess enjoyment of physical activity
**Intervention adherence**		
	MBE^a^ adherence	Track MBE class attendance, online video tutorial use, and logs of home practice
	Web platform usage	Track logins to the website, clicks on education links, downloads and views of videos, and pedometer use

^a^MBE: mind–body exercise.

In addition, all participants will undergo testing to collect exploratory outcome measures at baseline, month 3 and 6 in-person, and month 9 and month 12 by phone. Table 3 outlines exploratory patient-centered outcomes including cognitive-behavioral and psychosocial measures, overall physical activity, disease-specific HRQL and symptoms, and physical function and exercise capacity.

At each time point, we will administer questionnaires and collect physical activity data. At in-person visits only, we will additionally perform the 6-minute walk test. All tests will be conducted by study staff who will be blinded to treatment assignment. We will also track potential adverse events and COPD- and HF-related exacerbations and hospitalizations at each testing visit to assess safety.

Qualitative interviews at 6 months and 12 months will further assess facilitators and barriers to participation and acceptability of the intervention and its multiple components. Additional questions will be guided by our conceptual model and explore themes of motivation, goal attainment, social support, self-reflection, and personal transformation.

**Table 3 table3:** Patient-centered outcomes.

	Measure	Description
**Cognitive–behavioral and psychosocial**		
	Self-Efficacy for Exercise Scale [106]	9-item validated scale from McAuley’s original barriers scale
	Self-Efficacy for Managing Chronic Disease Scale [107]	6-item subscale from the Chronic Disease Self-Management Study
	Intrinsic Motivation Inventory [108]	22-item validated scale with 4 subscales: interest/enjoyment, perceived competence, perceived choice, and pressure/tension
	Patient Activation Measure [109]	13-item short form validated scale from Insignia Health
	Medical Outcomes Study Social Support Survey [110]	20-item validated scale with 5 subdomains of tangible support, emotional support, informational support, affectionate support, and positive social interaction
	Multidimensional Assessment of Interoceptive Awareness [111]	32-item validated scale with 5 subscales of body sensations, emotional reaction/attentional response, attention regulation, mind–body integration, trusting body sensations, assessing 8 domains of body awareness
	CES-D^a^ [112]	20-item validated scale; participants with CES-D score > 20 will be referred back to primary provider for evaluation
**Physical activity**		
	Community Healthy Activities Model Program for Seniors Physical Activity Questionnaire [113]	41-item validated scale with leisure, household, occupational physical activity domains; allows estimation of weekly caloric expenditure
	Pedometer [114]	Step counts measured by Fitbit pedometer; device worn during waking hours except when showering/bathing
**Disease-specific HRQL^b^**		
	St. George’s Respiratory Questionnaire [115,116]	Respiratory-specific extensively validated measure of HRQL; total score and subscales of activity, symptoms, and impact
	Minnesota Living with HF^c^ [117]	HF disease–specific extensively validated measure of HRQL
	mMRC^d^ Dyspnea scale [118]	5-item scale assessing breathlessness (part of BODE^e^ index)
**Physical function and exercise capacity**		
	PROMIS^f^ Physical Function, Fatigue [119]	Short form 7-10 items; from NIH^g^ toolbox PROMIS
	6-minute walk test [120]	Distance walked in 6 minutes as a measure of exercise capacity, performed according to ATS^h^ guidelines; subjects will use supplemental oxygen if already prescribed oxygen during activity

^a^CES-D: Center for Epidemiological Studies Depression scale.

^b^HRQL: health-related quality of life.

^c^HF: heart failure.

^d^mMRC: Modified Medical Research Council.

^e^BODE: body-mass index, airflow obstruction, dyspnea, and exercise.

^f^Patient-Reported Outcomes Measurement Information System.

^g^NIH: National Institutes of Health.

^h^ATS: American Thoracic Society.

#### Statistical Analysis

For study feasibility and intervention adherence, we will use descriptive statistics to evaluate recruitment and retention rates, attendance at mind–body exercise classes, and adherence with the online intervention (web-platform usage). We will consider study retention successful if the retention rate is at least 80% and if attendance at in-person classes is at least 70% (17/25 classes). Mean scores on the Physical Activity Enjoyment Scale at each time point will be reported [105].

To further evaluate intervention acceptability, 6-month and 12-month qualitative interviews will be recorded and transcribed verbatim. Thematic analysis will be informed by grounded theory methods based on our semistructured questions. Transcripts will be independently coded by at least 2 separate investigators to identify emergent themes in an iterative process until thematic saturation is reached. We will particularly search for themes that may give insights into factors mediating a shift in self-efficacy towards longer-term maintenance of walking and overall physical activity.

For each patient-centered outcome, repeated measures analyses will be performed using SAS PROC MIXED to evaluate trajectories over the course of the 4 time points for each group and the differences between the groups in these trajectories at each time point. Planned paired comparisons and Cohen’s d effect sizes will also be computed to evaluate the magnitude of improvement between time points and group differences in change. These data will provide valuable information including what outcome domains and measures may demonstrate clinically meaningful changes in future models, the appropriate number of time points to use in a future clinical trial, and measures of variability within and between groups to inform the design of future studies. Measures considered sensitive to change will be those that indicate trends in improvement over time.

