## Results

Mindful Steps was funded in February 2017, approved by the institutional review board at Beth Israel Deaconess Medical Center in January 2017 and at the University of Michigan in May 2017. Phase I intervention development was completed in March 2019, phase II data collection began in April 2019, and completion is expected by August 2021. A total of 41 subjects have been enrolled.

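### The success rule for study retention includes class attendance, which Table 2 treats as adherence, so the article's two retention rules can give opposite verdicts; neither sets a condition by arm

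*Protocol article*

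**What the plan says.** The protocol article gives two rules for judging retention.

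- **Statistical Analysis:** "We will consider study retention successful if the retention rate is at least 80% and if attendance at in-person classes is at least 70" per cent. The same sentence then gives the attendance threshold as a count: "attendance at in-person classes is at least 70% (17/25 classes").
- **Table 2, Study feasibility:** "Track retention rate with acceptable retention defined as <20% dropouts". There is no attendance condition.

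Table 2 places attendance under a different heading, Intervention adherence: "Track MBE class attendance, online video tutorial use, and logs of home practice".

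Two further statements bear on the point. Randomization and Intervention Delivery assigns the class schedule to one arm: "Participants in the Mindful Steps intervention will receive the pedometer, access to the Mindful Steps website, and a schedule of in-person mind–body exercise classes". The introduction to Phase 2 gives the size and allocation: "42 participants with COPD and/or HF have been randomized in a 2:1 ratio". The Results section gives a slightly different number: "A total of 41 subjects have been enrolled".

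**The concern.** Retention asks whether participants stay under follow-up. Attendance asks whether those offered the classes use them. A Mindful Steps participant can complete every assessment and skip most classes, and a usual-care participant has no attendance value at all. Joining the two under the name of study retention gives a verdict that does not show which part failed. It also conflicts with Table 2.

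The rule also names one retention rate and no threshold by arm. Under 2:1 allocation the usual-care arm is a third of the sample, so heavy loss there moves the overall rate only modestly. The attendance condition gives some indirect check on Mindful Steps but none on usual care.

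The pilot is meant to inform the design of a larger trial. A planner needs to know separately whether participants can be followed for a year in each arm and whether the classes are attended.

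**Working it through.** **Inputs.** N = 42, allocation 2:1 (Phase 2 introduction), so 28 Mindful Steps and 14 usual care. Alternative N = 41 (Results). Retention threshold 80% and attendance threshold 70%, given as 17/25 (Statistical Analysis). Dropouts below 20% (Table 2).

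**1. The plan's own attendance figure.** 17/25 = 68.0%, which is below 70%. Since 0.70 × 25 = 17.5, the smallest whole number of classes reaching 70% is 18 (18/25 = 72.0%). The stated count does not reproduce the stated percentage. The denominator is also unsettled: the schedule under Component 6, counted plainly, gives 6 + 34/2 + 12/4 = 6 + 17 + 3 = 26 classes, while the stated total is 25.

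**2. Do the two retention thresholds agree without attendance?**

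| N | Fewest retained at 80% or more | Losses allowed | Dropout rate at that limit | One more loss |
|---|---|---|---|---|
| 42 | 0.80 × 42 = 33.6, so 34 (81.0%) | 8 | 8/42 = 19.0% | 33/42 = 78.6%, fails |
| 41 | 0.80 × 41 = 32.8, so 33 (80.5%) | 8 | 8/41 = 19.5% | 32/41 = 78.0%, fails |

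They agree at either N. Any conflict comes from the attendance clause alone.

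**3. Opposite verdicts on the same data.** Take 42/42 retained and attendance of 69%.

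- Table 2: 0% dropouts, so acceptable.
- Statistical Analysis: 69% is below 70%, so not successful.

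This example uses the stated percentage. If the threshold is read as 17/25, attendance has to fall below 68% for the conflict to appear.

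**4. No condition by arm.** Place all 8 allowed losses in usual care, with attendance met.

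| Split | Controls lost | Controls kept | Rule |
|---|---|---|---|
| 28:14 | 8/14 = 57.1% | 6/14 = 42.9% | met |
| 27:14 | 8/14 = 57.1% | 6/14 = 42.9% | met |
| 28:13 | 8/13 = 61.5% | 5/13 = 38.5% | met |

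**5. The attendance denominator matters.** Suppose all 8 losses are in Mindful Steps. As an illustration only, assume that completers attend 85% of classes and dropouts 20%.

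- Completers only: 85%, so the attendance condition is met.
- All 28 randomised, with classes after dropout counted as missed: (20 × 85 + 8 × 20)/28 = 1860/28 = 66.4%, so it is not met.

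The article does not say which denominator applies, or whether 17/25 is a group mean or a threshold for each participant.

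**6. Precision at the threshold.** The Wilson 95% confidence interval for 34/42 is 66.7% to 90.0%.

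**The case against.** The strongest reply is that this is a labelling fault in a descriptive pilot criterion. The same section says that recruitment, retention, attendance and web use will each be described, so the components would be visible whatever the joint verdict. No stop or go decision is attached to it, and reporting by arm is a detail an article commonly leaves to the full protocol. This limits the consequence, and it means that the absence of a promise to report by arm is not in itself a fault. It does not remove the conflict, because both rules are stated in the article and disagree.

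Four stronger readings are tempting, and the documents do not support them.

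- **That the rate is explicitly pooled, so loss in one arm could not be seen.** A single overall rate is the plain reading, but it is inferred. Nothing rules out reporting by arm.
- **That the rule would also pass with all 8 losses in Mindful Steps (20/28 = 71.4% kept).** It passes only if attendance is met. Step 5 shows that the joint rule can fail in that case.
- **That unequal loss would bias every comparison between arms.** Unequal loss can bias a comparison but does not establish bias. The patient-centred outcomes are exploratory, and the planned mixed model uses incomplete records.
- **That a minimum retention in each arm is required.** The documents give no basis for one. A floor of 70%, for instance, would still pass 20/28.

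Losing 8 of 14 controls and nobody else is also the most extreme arrangement possible. It shows what the rule permits, not what is likely.

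**Conclusion.** The concern holds in a limited form. The article states two retention rules that can disagree on the same data, and the cause is an adherence measure, available in one arm only, placed inside a verdict on the whole study. The numerical retention limits themselves agree, at 8 losses for N = 42 or 41.

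The lack of a condition by arm is a secondary weakness. It assumes that the 80% is one overall rate, that the split is about 28:14 and that attendance is met. On those assumptions, usual care could fall to 43% retained (38% if the split is 28:13) with the rule still satisfied.

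The attendance threshold is wrong as written, because 68% is presented as 70%. No planned comparison of outcomes is changed by any of this. What is affected is the feasibility conclusion that would be carried into the next trial.

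**What to change.** Replace the single sentence in Statistical Analysis with two criteria, and use the same wording in Table 2.

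- **(a) Retention:** at least 80% of all randomised participants retained, reported overall and by arm with 95% confidence intervals.
- **(b) Adherence:** class attendance of at least 70% among all participants randomised to Mindful Steps, with classes after dropout counted as missed.

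For (b), reconcile 70% with 17/25 (70% of 25 needs 18 classes), confirm the total number of classes, and say whether the threshold is a group mean or applies to each participant. For (a), reconcile the 42 randomised with the 41 enrolled so that the denominator is fixed.

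This needs no new data and no change in conduct. The cost is that success criteria are clarified after randomisation and while data are being collected, so the change should be dated and disclosed when results are reported.

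### The attendance criterion contradicts itself: 17 of 25 classes is 68%, below the stated 70% minimum, and the class total of 25 holds only on one reading of the schedule

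*Protocol article*

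**What the plan says.** The Statistical Analysis section of the protocol article names two numeric conditions for success: retention of at least 80%, and a minimum level of attendance, given as "attendance at in-person classes is at least 70% (17/25 classes". The bracket turns the percentage into a number of classes.

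The denominator comes from the section on Component 6, Live Group Classes, which gives the schedule and its total: "Classes are conducted weekly for the first 6 weeks, biweekly for the next 34 weeks, and monthly for the last 12 weeks (25 total". Both sections therefore use 25 as the number of classes.

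The Statistical Analysis section says that feasibility and adherence will be summarised with descriptive statistics. The Study Assessments section says that these measures are tracked to inform a later, larger trial.

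**The concern.** A threshold fixed in advance should give one answer for any result. Here the percentage and the count are offered as the same rule, but the count lies below the percentage. A result of 17 classes out of 25 is a success by the bracket and a failure by the percentage, so someone must choose between them, possibly after seeing the data. Attendance is one of only two numeric success conditions in this section, and feasibility is the purpose of the pilot.

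The denominator raises a second question. On a plain reading, the three blocks of the schedule do not add up to the printed total. If a different number of classes is offered, the count that corresponds to 70% changes too.

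**Working it through.** **Inputs**

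- Threshold: at least 70%, also printed as 17 of 25 (Statistical Analysis).
- Schedule: 6 weeks weekly, 34 weeks biweekly, 12 weeks monthly, total printed as 25 (Component 6).

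**Step 1: does 17 of 25 meet the 70% rule?**

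- 17/25 = 0.680, or 68.0%. This is 2.0 percentage points short, so the printed equivalence is not reproduced.
- 0.70 × 25 = 17.5. The smallest whole number at or above this is 18, and 18/25 = 72.0%.
- Rounding does not rescue the figure. Rounding 17.5 down breaks a rule worded as a minimum, and conventional rounding also gives 18.

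**Step 2: when do the two forms disagree, with 25 classes?**

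- Applied to each participant: only at exactly 17 classes. At 16 or fewer both fail; at 18 or more both pass.
- Applied to the group mean: from 17.0 up to, but not including, 17.5 classes (68% to just under 70%).

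**Step 3: does the schedule give 25 classes?**

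- Block lengths: 6 + 34 + 12 = 52 weeks, which fits a one-year programme.
- Weekly block: 6/1 = 6 classes.
- Biweekly block, read as every two weeks: 34/2 = 17 classes, whether it starts in week 7 or week 8. Read as twice a week it would hold 68, for a total of 6 + 68 + 3 = 77, which cannot be meant.
- Monthly block, read as every four weeks: 12/4 = 3 classes, for example in weeks 41, 45 and 49 or in weeks 44, 48 and 52.
- Total: 6 + 17 + 3 = 26, one more than printed.
- Alternative: take monthly as a calendar month of 365.25/12/7 = 4.35 weeks, counted from a last biweekly class in week 40. Classes then fall at about weeks 44.3 and 48.7, and the next at week 53 is outside the year. The block holds 2 classes and the total is 6 + 17 + 2 = 25, as printed.
- Calendar-month spacing alone is not enough. If the first monthly class is in week 41, the block again holds three (weeks 41, 45.3 and 49.7), for a total of 26.

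**Step 4: what follows if 26 classes are offered (conditional on that reading)?**

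- 17/26 = 65.4% and 18/26 = 69.2%; both fall short of 70%.
- 0.70 × 26 = 18.2, so 19 classes are needed, and 19/26 = 73.1%.

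**The case against.** The strongest reply is that this is a one-class slip in an explanatory bracket. Since 70% of 25 is not a whole number, 17 looks like 17.5 rounded down. The figure drives no sample size, test, error rate or stopping rule. Observed attendance will be described whichever label is attached, and the range in which the labels differ is narrow. All of this stands and limits the weight of the point. It does not make 17 of 25 meet a 70% minimum, and nothing elsewhere in the article settles which form governs.

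A reader might infer that the decision to proceed to a larger trial hangs on this discrepancy. The article does not support that: it says when the result will be considered successful, but gives no progression rule.

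A reader might also infer that the total of 25 is simply wrong. That is too strong. The figure of 26 rests on reading monthly as every four weeks, which the article does not say, and 25 is reached if the last block holds only two classes. Both sections use 25, so the denominator is at least used consistently. The 26-class figures are conditional and are less certain than the 68% result.

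Finally, it cannot be assumed that the percentage was intended and the count is the mistake. The target may have been 17 classes, loosely described as 70%. The documents do not show which.

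**Conclusion.** The attendance criterion is wrong as written. With the printed denominator of 25, the count is 68.0% against a stated minimum of 70%, and the first count that meets the minimum is 18. This part is exact and rests on no assumption about the schedule.

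The consequence is minor: the success label is ambiguous for one whole-number result per participant, or for a half-class range of the group mean, in a descriptive criterion.

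The mismatch between schedule and total is a request for clarification. It is a one-class discrepancy if monthly means every four weeks, and none if the last 12 weeks hold two classes.

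**What to change.** Before analysis:

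1. State the criterion so that percentage and count agree. If 70% is the intended rule, write at least 18 of 25 classes, or at least 19 of 26 if 26 are offered. If 17 of 25 was the intended target, the percentage printed beside it should be 68%.
2. Define the denominator as the number of classes actually offered.
3. Reconcile the Component 6 schedule with its printed total, for example by stating how many classes the last 12 weeks contain. Which schedule is right is for the investigators to say; this review takes no position.

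The cost is a corrected sentence in Statistical Analysis and a clarification under Component 6. If the 70% rule is kept, the threshold becomes one class stricter than the printed count with 25 classes (18 instead of 17), or two classes stricter with 26 (19 instead of 17).

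### Between-group effect sizes are planned on change scores with no stated baseline adjustment; a baseline-adjusted contrast would usually be more precise at very small cost

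*Protocol article*

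**What the plan says.** The Statistical Analysis section of the protocol article gives two analyses for each patient-centered outcome.

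- The first is a mixed model: "repeated measures analyses will be performed using SAS PROC MIXED to evaluate trajectories over the course of the 4 time points for each group", together with "the differences between the groups in these trajectories at each time point". No covariate or baseline constraint is named, and none is excluded.
- The second is a set of paired comparisons and Cohen's d effect sizes, computed "to evaluate the magnitude of improvement between time points and group differences in change".

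Baseline is available. Under Study Assessments, staff "collect exploratory outcome measures at baseline, month 3 and 6 in-person, and month 9 and month 12 by phone", which makes five assessments against the four time points of the model. The same section calls these "exploratory patient-centered outcomes including cognitive-behavioral and psychosocial measures". The Phase 2 section states that "42 participants with COPD and/or HF have been randomized in a 2:1 ratio". The Statistical Analysis section adds that the results, including within- and between-group variability, are meant to inform the design of later studies.

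**The concern.** A change score uses the baseline, but it fixes the baseline slope at 1. When the true slope is smaller, the change score over-corrects. Part of any chance baseline difference between the arms then passes into the estimated group difference with the opposite sign. In a trial of about 42 people allocated 2:1, chance differences at baseline can be sizeable.

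The mixed model does not clearly avoid this. The four time points can be read in three ways:

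1. Baseline and three follow-ups are responses in an ordinary group-by-time model. With complete data, the group contrast then equals the change-score difference, and one follow-up is left out.
2. The four follow-ups are the responses, with no baseline covariate. Baseline is then unused in the model.
3. The four follow-ups are the responses, with baseline as covariate. The model is then already efficient, but Cohen's d is still computed on change.

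Under each reading, something in the section should be changed or stated. What is at stake is the precision of between-group estimates that the next trial's designers are expected to use.

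**Working it through.** **Plan's own figure.** The article gives no power, SD, effect size or precision target for these outcomes, so there is nothing to reproduce.

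**Inputs**
- Sample size 42 at 2:1 (Phase 2 section), giving 42 x 2/3 = 28 and 42/3 = 14. The split is derived, not printed. The Results section says "A total of 41 subjects have been enrolled"; one participant fewer does not change the picture.
- rho, the baseline to follow-up correlation, is not in the documents. It is assumed and shown from 0.3 to 0.9.
- Equal SDs at baseline and follow-up are assumed. All results are in SD units.

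**Formulas**, with h = 1/28 + 1/14 = 0.107:
- Change-score difference: variance = 2(1 - rho)h
- Baseline-adjusted difference: variance = (1 - rho^2)h x [1 + 1/(N - 4)]. The bracket is the cost of estimating the slope: 1 + 1/38 = 1.026.
- Ratio, adjusted to change: [(1 + rho)/2] x 1.026

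Example at rho = 0.5:
- Change: 2 x 0.5 x 0.107 = 0.107, SE 0.327.
- Adjusted: 0.75 x 0.107 x 1.026 = 0.082, SE 0.287.
- Ratio: 0.75 x 1.026 = 0.770, a 23% reduction.

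| rho | SE, change | SE, adjusted | Variance ratio | Variance cut | CI width ratio |
|---|---|---|---|---|---|
| 0.3 | 0.387 | 0.316 | 0.667 | 33% | 0.817 |
| 0.5 | 0.327 | 0.287 | 0.770 | 23% | 0.878 |
| 0.6 | 0.293 | 0.265 | 0.821 | 18% | 0.907 |
| 0.7 | 0.254 | 0.237 | 0.872 | 13% | 0.935 |
| 0.8 | 0.207 | 0.199 | 0.924 | 8% | 0.962 |
| 0.9 | 0.146 | 0.145 | 0.975 | 2-3% | 0.988 |

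CI widths use t quantiles with N - 2 degrees of freedom (change) and N - 3 (adjusted).

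**Checks.** Simulation of 20,000 trials at 28:14 gave variance ratios of 0.67, 0.76, 0.87, 0.97 and 1.00 at rho 0.3, 0.5, 0.7, 0.9 and 0.95. With about 80% retained (22:11), the formula ratios at the six tabled values of rho are 0.67, 0.78, 0.83, 0.88, 0.93 and 0.98. The two methods break even where (1 + rho)/2 x 1.026 = 1, at rho of about 0.95.

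**The same loss seen as chance imbalance.** The baseline difference D has SE sqrt(0.107) = 0.33 SD. Given D, the change-score estimate shifts by -(1 - rho)D. At rho 0.6, a one-SE imbalance shifts it by 0.4 x 0.33 = 0.13 SD. The excess variance of the change score before the slope cost is 2(1 - rho)h - (1 - rho^2)h = (1 - rho)^2 h, which is exactly the variance of that shift. Lost precision and carried-over imbalance are therefore one quantity and must not be added together.

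**The case against.** The strongest reply is that the article is condensed and its full analysis plan is not shown. Covariate terms are commonly left to that plan, and four time points could mean four follow-ups with baseline as covariate. This stands as far as the mixed model goes. A reader might infer that the model leaves baseline out, but the text is silent and does not support that. The reply does not reach the effect sizes, where a group difference in change is stated outright. It also does not remove the mismatch between five assessments and four time points.

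It can further be said that a difference in change names a quantity and not an estimator, since a constrained-baseline model also estimates one. That is fair. But Cohen's d beside paired comparisons is most naturally a raw change-score computation, and nothing in the section points elsewhere.

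Two more objections stand. The gain rests on an assumed rho and is negligible near 0.9. The outcomes are exploratory in a feasibility pilot whose success criteria are retention and attendance, so no formal conclusion depends on this choice.

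A reader might also infer that the change-score estimates are biased. Under randomization they are not: the shift averages to zero over allocations and appears only given the imbalance that happened to occur.

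**Conclusion.** The point holds as an efficiency recommendation. The stated change-score contrast is less precise than a baseline-adjusted one for rho up to about 0.95. At rho 0.5 to 0.7 the variance cut is 23% to 13%, and the CI narrows by about 12% to 6%. At rho 0.9 the cut is only 2-3%. These sizes rest on the assumed rho, on equal SDs and on the derived 28:14 split.

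It would go too far to call the adjustment free, or the gain material for every outcome. It costs a degree of freedom and a variance factor of about 1.03, and the documents give no correlation from which to show that the gain is material for any particular scale. For the mixed model, the supported statement is that the handling of baseline is not stated and the time-point count does not match the assessment schedule.

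**What to change.** 1. State how baseline enters PROC MIXED. Either make baseline one of the five responses, with a common baseline mean across arms and group-by-time effects from month 3 on, or model the four follow-ups with baseline-by-time as covariate. With complete data the two agree closely; with missing data they are only approximately equivalent.
2. Correct the time-point count to match the chosen model. The 6-minute walk test is done only at in-person visits (baseline, months 3 and 6), so its model has three responses, or two follow-ups with baseline as covariate.
3. Report the adjusted group difference at each follow-up, divided by the pooled baseline SD, with its 95% CI, instead of or beside the change-score d. Naming the standardizer matters: dividing by the SD of change instead multiplies d by 1/sqrt(2(1 - rho)), which is 0.85 at rho 0.3 and 1.29 at rho 0.7.

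This needs a few lines of wording and code and no new data. The statistical cost is the one given in the verdict. A fixed effect for diagnosis group is optional and not part of this point.
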